### Concealment mechanism {16b}

Not applicable as this is an open-labelled nutrition supplementation study.

### Implementation {16c}

The allocation sequence is generated by [name] as an investigator who is not involved in the recruitment and the enrolment of the patients. [name] as the graduate research assistant enrols and assigns patients to interventions. [name] is not aware of the sequence and order of assignment ahead of time and will acquire the subject randomisation code from [name] upon each successful enrolment.

## Assignment of interventions: blinding

### Who will be blinded {17a}

As this is an open-labelled study, the patients and investigators will not be blinded. Data will be analysed by the investigators; hence, this would not be blinded either.

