#### Postoperative complications

The postoperative complications are defined as any deviation from the normal postoperative course and divided into minor and major complications. Minor complications include minor risk events, such as wound infection, urinary tract infection, or postoperative ileus [43]. Major complications include potentially life-threatening complications and those with a need of surgical, endoscopic, or radiological intervention, such as an anastomotic leak, abdominal abscess, and pneumonia [43]. Any readmission to the hospital for 30 and 90 days after surgery is to be recorded including the length of hospital stay and reason of readmission.

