### Confidentiality {27}

Confidentiality of all study patients will be maintained where a patient ID for patient identification will be used on patients’ data sheets throughout the study. Patients’ names will be kept on a password-protected database.

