## Statistical methods

### Statistical methods for primary and secondary outcomes {20a}

Statistical analyses will be performed using the Statistical Package for the Social Science software (SPSS version 26, IBM, USA). The normality of the data will be evaluated using Shapiro-Wilk’s test. Normally distributed data will be expressed as mean and standard deviation. Skewed data will be described using median with interquartile range for skewed data. Categorical data will be expressed in count and percentages. Evaluation of outcomes will be carried out by both intention-to-treat and per-protocol analyses. The primary analysis will take a per protocol approach and the secondary analysis an intention-to-treat (ITT) approach. The per protocol analysis will include patients who fully completed the intervention allocated and attended all visits (‘complete cases’ approach). The primary analysis will employ repeated measures ANOVA (RMANOVA) to assess for time × group interactions. A secondary analysis of difference between groups for continuous variables will be conducted by using analysis of covariance (ANCOVA), controlling for baseline or at discharge values. The ITT approach will include all patients who are randomised to the three groups, irrespective of dropouts. In order to perform RMANOVA using the ITT approach, missing data will be imputed with the last observation carried forward method using the last available data point from the patients. ANCOVA will be restricted to per-protocol basis. *P*-value <0.05 is considered statistically significant for all tests.

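### The plan gives up blinded analysis only because investigators do it, which does not follow; the exposure that reaches the primary result is unblinded judgement of who enters the per-protocol set

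*Protocol article*

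**What the plan says.** All references are to the protocol article.

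- **Who will be blinded {17a}** first covers conduct: "As this is an open-labelled study, the patients and investigators will not be blinded". It then covers the analysis: "Data will be analysed by the investigators; hence, this would not be blinded either". No other reason is given for leaving the analysis unblinded.
- **Implementation {16c}** has the sequence generated by a person described "as an investigator who is not involved in the recruitment and the enrolment of the patients". The research assistant "will acquire the subject randomisation code from" that person at each enrolment.
- **Confidentiality {27}** states that "a patient ID for patient identification will be used on patients’ data sheets throughout the study".
- **Statistical methods {20a}** makes per protocol the primary approach and intention-to-treat the secondary one. The per-protocol set is "patients who fully completed the intervention allocated and attended all visits". The primary test is a repeated measures ANOVA (RMANOVA) for the time by group interaction.
- **Strategies to improve compliance {11c}** defines compliance as grammes consumed over grammes expected, from weighed cans. It gives no value at which a patient counts as having completed.

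**The concern.** Open-label delivery unblinds patients and staff. It says nothing about whether the person fitting the model must see which arm is which, so the inference in {17a} fails as written. This is a stated decision, not a detail left to another document.

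It would matter little if nothing remained to be judged. Here the primary analysis set depends on a completion status that the article does not reduce to a rule. Staff who know the arm will classify patients. They may also have seen outcomes: weight and BMI are obtained at visits, and entered data are cross-checked monthly (Data management {19}). In arms of this size, a few classifications can move a between-arm difference, and a reader could not exclude that this had happened.

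**Working it through.** **Step 1. Does the stated reason hold?** Masked analysis needs patient identifiers in place of names, a list linking them to arms, and someone outside recruitment to hold that list. {27} supplies the first. {16c} supplies the other two. Analysis by investigators is therefore compatible with coded arms.

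**Step 2. Which decisions reach the primary result?**

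| Decision | Section | Analysis affected | Open to judgement in this article? |
|---|---|---|---|
| Completion of the supplement | {20a}, {11c} | Primary | Yes: continuous ratio, no cut-off |
| Attendance at all visits | {20a} | Primary | No: factual |
| Choice of test | {20a} | Primary | No: RMANOVA, time by group |
| ANCOVA covariate | {20a}, Table 2 | Secondary | Probably not (see objection) |
| Minor or major complication | Postoperative complications | Secondary outcome | Somewhat, but the grader is not named |

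Only the first row is both open and primary.

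**Step 3. Is that judgement even across arms?** Intervention description {11a} gives 3 servings of 55 g, so 3 × 55 = 165 g a day. From the durations in {6b}:

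- Group DS: in-hospital days only.
- Group SS: 5 to 14 preoperative days, 5 × 165 = 825 g to 14 × 165 = 2,310 g, plus in-hospital days.
- Group SS-E: the same preoperative amount plus 90 × 165 = 14,850 g, so 15,675 to 17,160 g if the 90 days run from surgery.

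SS-E thus has by far the longest period over which completion must be judged, and expected grammes alone identify that arm. The denominator is also not settled. The abstract counts the 90 days from discharge and {6b} counts them postoperatively; the abstract gives only an upper limit for the preoperative days and {6b} gives a range. These passages must be reconciled before any ratio is computed.

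**Step 4. Illustrative size.** Inputs from Sample size {14}, taken as stated: 23 evaluable per group, SD 6.5 g/L, target difference 4 g/L. Assume that 2 patients' membership is in doubt and that both lie one SD from the rest, in the same direction.

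- Share of the arm: 2/23 = 8.7%.
- Shift in the arm mean: (2/23) × 6.5 = 0.57 g/L.
- Relative to target: 0.57/4 = 14%.
- Standard error of a between-arm difference: 6.5 × √(2/23) = 1.92 g/L, so the shift is 0.57/1.92 ≈ 0.3 standard errors.

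**Step 5. Worst-case bound.** Simulation with no true effect, two arms of 28, SD 6.5, two-sided t test at 5%, 20,000 runs, leaving out the k lowest values of one arm:

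| k left out | Type I error | Mean shift (g/L) |
|---|---|---|
| 0 | 4.9% | about 0 |
| 1 | 6.6% | 0.5 |
| 2 | 9.7% | 0.9 |
| 3 | 12.8% | 1.3 |
| 4 | 17.2% | 1.6 |
| 5 | 22.6% | 2.0 |

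This represents deliberate selection on the outcome, with a t test standing in for the planned RMANOVA. It bounds the damage and does not predict it. For scale, the plan itself allows for 28 − 23 = 5 losses per arm.

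**Step 6. Can membership be fixed early?** Cans are collected and weighed at succeeding visits ({11c}). Serum is frozen and assayed only after all five visits (Blood samples). A patient's completion status can therefore be settled before the albumin and prealbumin results exist. That protection does not extend to weight and BMI, which are known at each visit.

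**The case against.** A reader might infer that three unblinded judgements together decide the primary result: completion, the ANCOVA covariate and complication grade. The article does not support that.

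- ANCOVA is labelled secondary. Its covariate, "controlling for baseline or at discharge values", most naturally follows Table 2, where the discharge visit is compared with baseline and the two later visits with discharge. The text above that table refers everything to baseline, which is looser, but the table supplies the mapping.
- Complications are a secondary outcome, "defined as any deviation from the normal postoperative course and divided into minor and major complications", with examples of each class. The section does not say that analysts do the grading. If it happens during care or data collection, masking the analysis file would change nothing.

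A reader might also infer that masked analysis is the only safeguard left. It is not. Albumin and prealbumin are run on an automated analyser through a commercial laboratory, weight is measured twice on a calibrated scale, the primary test is named, and an intention-to-treat RMANOVA on all randomised patients can be set beside the per-protocol result.

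Nor does {17a} claim that blinding is impossible. It says only that the analysis would not be blinded.

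Two further objections carry weight. Expected grammes reveal the arm, so completion status cannot be judged fully masked. And a statistical analysis plan not shown may contain a compliance cut-off, which would remove much of the discretion.

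What survives is the failed inference in {17a} and, on this article's wording, unblinded discretion over membership of the primary set. The intention-to-treat analysis makes a discrepancy visible, but as a secondary analysis it does not replace the primary result. An unseen cut-off would reduce the exposure without reversing the stated choice to analyse unblinded.

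**Conclusion.** The concern holds in a limited form. The reason given for unblinded analysis is not a reason, and the choice matters chiefly because per-protocol membership is primary and rests on a ratio without a threshold. The ANCOVA covariate and the complication grade do not decide the primary result.

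The likely effect is modest: 0.57 g/L, or 14% of the target difference, if two patients per arm are in play and both lie one SD out in the same direction. That is an assumption for illustration. The simulated error rates apply only to deliberate selection. Nothing in the article suggests that biased classification is intended; the point is that the plan as written cannot exclude it, and that excluding most of it costs little. The conclusion assumes that no completion threshold is fixed elsewhere.

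**What to change.** Amend {17a} and {20a} together.

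1. State one numerical compliance rule that, with attendance at all visits, defines the per-protocol set. Apply it identically to every patient, after reconciling the passages that set expected intake.
2. Date and lock each patient's status before the stored-serum results are available and before any outcome data are joined to arm.
3. Have the investigator who holds the sequence prepare an analysis file with neutral arm codes, with compliance data kept in a separate file. That investigator should not run the primary analysis.
4. Break the code only after the primary RMANOVA is final.

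The cost is a recoded file, a dated lock note and a separation of tasks among existing personnel. The limitation should be stated openly: masking is partial, because expected grammes and supplementation duration differ by arm, so the fixed rule and the early lock do most of the work.

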### Procedure for unblinding if needed {17b}

The unblinding procedure is not applicable for the patients and graduate research assistant as they are not blinded from the intervention allocated.

## Data collection and management

### Plans for assessment and collection of outcomes {18a}

#### Malnutrition identification

The presence and classification of malnutrition are determined based on the A.N.D/A.S.P.E.N diagnostic characteristics for adult malnutrition (undernutrition) in the context of chronic diseases related to malnutrition [38]. It recommends six characteristics including insufficient energy intake, weight loss, loss of muscle mass, loss of subcutaneous fat, fluid accumulation, and diminished functional status as measured by handgrip strength. Energy intake is assessed with 24-h diet recall and compared against a 2000-kcal diet to determine the insufficiency of intake. Patients are also probed for the duration of adopting the current diet. Weight loss is calculated from the difference between usual and current body weight and expressed in percentage along with the period of weight loss. Loss of muscle mass is assessed based on the wasting of the temples, clavicles, shoulders, interosseous muscles, scapula, thigh, and calf muscles. Loss of subcutaneous fat is evaluated based on the depletion of fat around orbital, triceps, and ribs areas. Fluid accumulation is determined based on the evidence on extremities, vulvar/scrotal edema, or ascites. Reduced grip strength is assessed by comparing the grip strength measured by a hand dynamometer (Jamar Hydraulic Hand Dynamometer 5030J1, Sammons Preston Rolyan, USA) to the normative standards supplied by the manufacturer. Patients who exhibit at least 2 of the six characteristics meet the criteria for malnutrition. Patients are classified as severe malnutrition if ≥ 2 indictors in the severe category and patients are classified as moderate/non-severe malnutrition if ≥ 2 indictors in the moderate category or 1 in severe and 1 in moderate category [39].

#### Anthropometric measurements

Body weight is measured using a calibrated weighing scale (Tanita HD-325, Tanita Corporation, Japan) that measures up to 150kg with a graduation of 0.1kg. Patients are instructed to keep barefooted, stand upright, and remove all the removable items such as accessories and jackets prior to the measurement. Height is measured using a light-weight portable stadiometer (Seca 213, Seca, Germany) that measures up to 205cm with a graduation of 0.1cm. The measurement is taken barefooted with patients’ heads positioned in the Frankfurt plane. Both weight and height are repeated once to obtain the mean. Weight changes are determined based on the number of changes from each visit. Body mass index (BMI) is expressed as weight in kilogrammes divided by height in metres squared.

#### Body composition

The body composition profile such as muscle and fat mass are obtained using a validated 8-point multiple frequency bioelectrical impedance analyser (Seca mBCA 525, Seca, Germany). Prior to measurement, patients are instructed to be properly hydrated, empty their bladder, remove all the removable items, and lie down flat for at least 10 min to achieve body fluid equilibrium. Two electrodes are placed at each extremity and each electrode is connected to a cable to pass the current through the 8 points. Data on fat mass, fat-free mass, skeletal muscle mass, and total body water are collected.

#### Handgrip strength

Handgrip strength is obtained using an analogue hydraulic dynamometer (Jamar Hydraulic Hand Dynamometer 5030J1, Sammons Preston Rolyan, USA) that measures up to 90 kgF with a graduation of 1 kgF. Patients are seated upright with the elbow of the dominant hand maintained at 90° and then asked to squeeze the handle at maximum strength. Encouragement is provided as they are squeezing. The measurement is repeated three times with a 1-min interval. The highest value of the dominant hand is used for analysis.

#### Blood samples

A total of 8ml of blood is drawn using venepuncture by a phlebotomist. From the sample, 2ml is used for the analysis of full blood count where haemoglobin is analysed by an automated haematology analyser (Sysmex XS-500i, Sysmex Europe GmbH, Germany) through the haemoglobin detector using the sodium lauryl sulphate haemoglobin detection method. The remaining sample is centrifuged at 1300 relative centrifugal force for 10 min (Eppendorf Centrifuge 5810 ®, Eppendorf AG, Germany) to aliquot serum samples for other assays. The serum samples are stored at −80 °C and analysed after collection of all 5 visits. The assays of serum albumin, prealbumin, transferrin, and hs-CRP are performed using an automated sample analyser (Siemens Advia ® 1800 Clinical Chemistry System, Siemens Healthcare GmbH, Germany). Interleukin-6 assay is performed using another automated sample analyser (Siemens Immulite ® 2000 XPi immunoassay system, Siemens Healthcare GmbH, Germany). The process of storing and analyses is managed by an established commercial laboratory (Pantai Premiere Pathology, Ampang, Malaysia).

#### Salivary samples

A total of 1ml of salivary sample is collected from the patients using a container that is made up of materials inert to the composition of the saliva. Salivary cortisol level is analysed using the enzyme-linked immunosorbent assay (ELISA) kit based on the competition principle. The process of storing and analyses is managed by an established commercial laboratory (Pantai Premiere Pathology, Ampang, Malaysia).

#### Dietary intake

Dietary intake at baseline is assessed using 1-week diet history with the multiple-pass method [40] to acquire detailed descriptions and portions of foods and beverages consumed. Patients then record their food intake using 3-day food records 2 weeks prior to surgery, 30 days after surgery, and 90 days after surgery. The food records are appended with a sample record, household measure illustrations, and common photographic food portions to aid in quantifying the foods and beverages consumed by the patients. The dietary intake on the day prior to surgery and the day prior to being discharged from the hospital are assessed using the 24-h dietary recall method. The dietary data will be analysed using Nutritionist Pro diet analysis software (version 7.4.0, 2019, Axxya Systems LLC, USA). Nutrients are analysed based on the database from Nutrient Composition of Malaysian Foods [41], Energy and Nutrient Composition of Singapore Foods [42], and nutrition labels on manufactured food products.

#### Length of hospital stay

The length of hospital stay is calculated from the day of admission up to 1 day prior to being discharged from the hospital. The information is obtained from patients’ hospital records.

#### Postoperative complications

The postoperative complications are defined as any deviation from the normal postoperative course and divided into minor and major complications. Minor complications include minor risk events, such as wound infection, urinary tract infection, or postoperative ileus [43]. Major complications include potentially life-threatening complications and those with a need of surgical, endoscopic, or radiological intervention, such as an anastomotic leak, abdominal abscess, and pneumonia [43]. Any readmission to the hospital for 30 and 90 days after surgery is to be recorded including the length of hospital stay and reason of readmission.

#### Sleep quality

Sleep quality is interviewed using the Pittsburgh Sleep Quality Index (PSQI) questionnaire [44]. It consists of 19 self-rated questions to assess sleep quality on subjective sleep quality rating, sleep duration, sleep latency, habitual sleep efficiency, sleep disturbance, use of sleep medication, and daytime dysfunction. The response to each question is then rated on a 0–3 scale based on the predetermined scoring scheme. All scores obtained are computed to yield a global PSQI score ranging between 0 and 21. A cut-off score of 5 indicates poor sleep quality and higher scores indicate poorer sleep quality.

### Plans to promote participant retention and complete follow-up {18b}

Doctors in charge are scheduling the patients’ upcoming clinic appointments according to the visitation timepoints. In between, regular phone calls and text messages are also sent as reminders to patients of the next visitation. For patients who drop out from this study, data will be included as intention-to-treat.

### Data management {19}

A folder consisting of forms created based on the collection methods of the parameters will be prepared for each patient. Data will be recorded manually at the point of collection and entered into the password-protected Microsoft ® Excel sheets. Cross-checking the data entered into the Microsoft ® Excel sheets against the manual record to verify the accuracy and completeness of the data is performed on monthly basis. On completion of study, data stored in the computer will be copied to CDs before being erased. CDs and all the manually recorded data will be stored in a locked office of the lead investigator and maintained for a period of 7 years after the completion of the study. The CDs and data will be destroyed after that period of storage upon approval from sponsor and ethics committees.

### Confidentiality {27}

Confidentiality of all study patients will be maintained where a patient ID for patient identification will be used on patients’ data sheets throughout the study. Patients’ names will be kept on a password-protected database.

### Plans for collection, laboratory evaluation, and storage of biological specimens for genetic or molecular analysis in this trial/future use {33}

Not applicable as all biological specimens will be discarded and no future analysis will be done after this trial.

## Statistical methods

### Statistical methods for primary and secondary outcomes {20a}

Statistical analyses will be performed using the Statistical Package for the Social Science software (SPSS version 26, IBM, USA). The normality of the data will be evaluated using Shapiro-Wilk’s test. Normally distributed data will be expressed as mean and standard deviation. Skewed data will be described using median with interquartile range for skewed data. Categorical data will be expressed in count and percentages. Evaluation of outcomes will be carried out by both intention-to-treat and per-protocol analyses. The primary analysis will take a per protocol approach and the secondary analysis an intention-to-treat (ITT) approach. The per protocol analysis will include patients who fully completed the intervention allocated and attended all visits (‘complete cases’ approach). The primary analysis will employ repeated measures ANOVA (RMANOVA) to assess for time × group interactions. A secondary analysis of difference between groups for continuous variables will be conducted by using analysis of covariance (ANCOVA), controlling for baseline or at discharge values. The ITT approach will include all patients who are randomised to the three groups, irrespective of dropouts. In order to perform RMANOVA using the ITT approach, missing data will be imputed with the last observation carried forward method using the last available data point from the patients. ANCOVA will be restricted to per-protocol basis. *P*-value <0.05 is considered statistically significant for all tests.

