### Interventions

#### Explanation for the choice of comparators {6b}

Eligible patients are randomised into one of the three intervention arms: Group SS, Group SS-E, and Group DS. Patients in Group SS will consume the ONS ranging from 5 to 14 days in addition to their normal diet preoperatively and postoperatively up to discharge from the hospital. Patients in Group SS-E will consume the ONS ranging from 5 to 14 days in addition to their normal diet preoperatively, post-operatively up to discharge from the hospital, and for an extended period of 90 days post-operatively. Group DS is the usual care group who will follow their normal diet preoperatively and only consume ONS in addition to their normal diet postoperatively up to discharge from the hospital.

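### The primary analysis is a completer analysis with ITT only secondary, although what patients must complete differs greatly by arm

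*Protocol article*

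**What the plan says.** Section {20a} of the protocol article fixes the order of the analysis populations: "The primary analysis will take a per protocol approach and the secondary analysis an intention-to-treat (ITT) approach". It defines the first: "The per protocol analysis will include patients who fully completed the intervention allocated and attended all visits". It defines the second as everyone randomised: "The ITT approach will include all patients who are randomised to the three groups, irrespective of dropouts". The primary test is the time × group term of a repeated-measures ANOVA. For ITT, "missing data will be imputed with the last observation carried forward method using the last available data point from the patients". A secondary ANCOVA adjusts for the baseline or the discharge value, and "ANCOVA will be restricted to per-protocol basis".

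Section {18b} adds: "For patients who drop out from this study, data will be included as intention-to-treat". Under {20a} this serves only the secondary analysis.

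Section {6b} sets what each arm has to complete. DS takes the supplement from surgery to discharge. SS also takes it for 5 to 14 days before surgery. SS-E does both and continues "and for an extended period of 90 days post-operatively". Section {11a} sets three servings a day. The trial is open-label, and the investigators who analyse the data are not blinded ({17a}). The sample size in {14} is built on detecting a between-group difference in albumin. No reason is given for putting the per-protocol set first.

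**The concern.** Randomisation makes the arms comparable as randomised. It does not make completers comparable, because completing is something that happens after allocation and may depend on appetite, tolerance of the supplement and recovery. Those factors plausibly bear on weight and albumin, which are primary outcomes.

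The problem is sharper here because the completion requirement is not the same in each arm. SS and SS-E are treated alike until discharge. After that, an SS patient stays in the primary set by attending visits, while an SS-E patient must also keep taking the supplement for the extended period. The comparison meant to show whether extended supplementation helps is therefore the one most exposed. In a trial looking for a difference, there is no non-inferiority argument for leading with completers.

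The ITT analysis as written is a weak safeguard. With last observation carried forward, a value from the day before discharge can stand in for day 90. The covariate-adjusted ANCOVA is not run on all randomised patients at all.

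**Working it through.** **Is the order reversed or explained elsewhere?** No. {18b} and {20c} describe the ITT set and its imputation, and neither makes it primary. {20a} is the only statement of priority.

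**How many patients leave the primary set?** The document gives one figure, 20% drop-out, applied equally to each group ({14}). Then 84 × 0.8 = 67.2, so about 17 of 84 randomised patients are left out, and 28 × 0.8 = 22.4 remain per arm. No completion rate by arm is given. The derivation of the sample size itself is a separate matter and is not used here.

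**What could differential completion do?** The plan has no figure to reproduce, so this is an illustration.

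- From the document: SD of albumin 6.5 g/L, 28 randomised per arm, target difference 4 g/L ({14}).
- Assumed: no true effect; a latent tendency to complete that correlates r = 0.3 to 0.5 with albumin, with better outcomes among completers; non-completion fraction d by arm.

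Mean shift among completers in one arm = r × 6.5 × λ(d), where λ(d) = φ(z_d)/(1 − d), φ is the standard normal density and z_d is the normal quantile at d.

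λ(0.10) = 0.1950; λ(0.15) = 0.2743; λ(0.25) = 0.4237; λ(0.30) = 0.4967; λ(0.40) = 0.6439.

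Bias = r × 6.5 × [λ(d in SS-E) − λ(d in DS)]. For 40% v 10% and r = 0.5: 0.5 × 6.5 × 0.4489 = 1.46 g/L. The false-positive rate is that of a two-sided 5% normal test with standard error 6.5 × √(1/n₁ + 1/n₂), where n = 28 × (1 − d).

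| Non-completion, SS-E v DS | λ difference | Bias, r = 0.3 | Bias, r = 0.5 | False-positive rate |
|---|---|---|---|---|
| 20% v 20% | 0 | 0 | 0 | 5.0% |
| 25% v 15% | 0.149 | 0.29 g/L | 0.49 g/L | 5.3% to 5.7% |
| 30% v 10% | 0.302 | 0.59 g/L | 0.98 g/L | 6.0% to 7.9% |
| 40% v 10% | 0.449 | 0.88 g/L | 1.46 g/L | 7.1% to 11.0% |

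The first row also assumes the same selection mechanism in both arms.

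**Does this carry over to the primary test?** Only in part. The table concerns albumin level, whereas Table 2 of the article and the time × group term concern change. With the same SD at two visits and correlations r₁ (earlier) and r₂ (later), the bias in change is (r₂ − r₁) × 6.5 × the λ difference. If r₁ = r₂, it is zero. With baseline-adjusted ANCOVA, r₁ = r₂ = r and a between-visit correlation ρ, about (1 − ρ) of the level shift remains. At an assumed ρ = 0.5 the 40% v 10% row becomes about 0.44 to 0.73 g/L. The document gives neither the correlation of completion with change nor the SD of change.

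**The case against.** Several points on the other side stand.

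- The protocol's only attrition figure is 20%, the same in each group. At equal non-completion with the same selection mechanism the illustrated bias is zero. The unequal rates are assumptions.
- Attending all visits is required in every arm, and so is withdrawal after a serious adverse event ({11b}, {22}). SS and DS differ by only 5 to 14 preoperative days. The unequal requirement is mainly a matter of SS-E.
- A reader might infer that the bias must favour SS-E. The document does not support that. It needs non-completers to be the sicker patients; patients who have recovered well may also stop a 90-day supplement, which would turn the sign.
- A reader might take the worst row of the table, 1.46/4 = 36% of the 4 g/L target, as the bias in the primary analysis. It is a shift in level under assumed 40% v 10% non-completion, and the primary test is on change. Likewise, an SS-E set of about 17 (0.6 × 28 = 16.8) only restates the 40% assumption.
- A reader might infer that no analysis that takes account of baseline respects randomisation. That goes too far. The ITT repeated-measures ANOVA is prespecified on all randomised patients, and its time × group term compares change over visits. What is missing is a covariate-adjusted comparison in that set, and an imputation that can be relied on.
- {18b} is not in conflict with {20a}. It confirms that dropouts' data are kept for ITT.

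None of this defends the order of the populations. The abstract speaks of effectiveness, so an explanatory aim cannot easily be pleaded for leading with completers.

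**Conclusion.** The point holds for the order of the analysis populations, and on that it is certain: {20a} states it outright, nothing reverses or justifies it, and {6b} makes completion a much longer requirement in SS-E than in SS or DS. The primary result would compare subsets formed after randomisation, with a completion rule that differs by arm.

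The size and direction of the bias are not established. On the stated assumptions (albumin level, SD 6.5 g/L, no true effect, r = 0.3 to 0.5) it runs from zero at equal non-completion and like selection, through 0.3 to 0.5 g/L at 25% v 15%, to 0.9 to 1.5 g/L at 40% v 10%. It would be smaller for change from baseline if completion is related to albumin about equally at each visit. The case for changing the plan does not depend on these figures.

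**What to change.** In {20a}:

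1. Make the primary analysis all randomised patients in their allocated arm, using all observed data.
2. Name a workable model: a likelihood-based mixed model for repeated measures, or multiple imputation, adjusted for the baseline value. This replaces repeated-measures ANOVA with last observation carried forward. Swapping the labels alone is not enough, because that ANOVA cannot use incomplete patients and the carried-forward analysis would become primary.
3. Make the completer analysis supportive.
4. Delete the sentence "ANCOVA will be restricted to per-protocol basis". Adjust the all-randomised comparison for baseline and not for the discharge value, which is measured after randomisation. The changes from discharge in Table 2 can be read off as contrasts between visits in the same model.

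The cost is a change of wording and of model, with no extra patients or visits. Section {21b} puts all analyses at the end of the study, so the order can be settled before outcomes are compared by arm. If adherence is poor, the all-randomised estimate will be somewhat diluted; the supportive analysis still describes the adherent patients. Patients withdrawn from the study may have no later data, so the new primary analysis would rest on a missing-at-random assumption, which should be stated.
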